## Introduction

### Rationale

Knee osteoarthritis (OA) is a leading cause of pain, functional disability and is a substantial economic burden on society and healthcare systems.^1–3^ Treatment guidelines for chronic knee pain in OA are mainly focused on pain management with a combination of pharmacological and non-pharmacological treatment approaches, but no disease-modifying treatment currently exists.^4^ Total knee replacement (TKR) is the ultimate treatment to alleviate pain, nevertheless chronic pain is still reported in about 20% of patients after the surgery.^5^ Currently, there is no objective protocol to detect how a patient will respond to a given OA treatment. Moreover, there is also a poor correlation between the severity of joint damage and severity of pain,^6^ which points to the contribution of central pain mechanisms.

Painful peripheral stimuli may alter the central nociceptive pathways leading to central sensitisation that can influence treatment response in patients with OA.^7^ Sensitisation, which plays a key role in augmenting OA pain, is defined as a modified perception of pain due to increased impulses from the peripheral nervous system (peripheral sensitisation) along with augmentation of pain signals in the central nervous system (central sensitisation).^8^ Central sensitisation was estimated to be present in about 30% of patients with OA^9^ and was found to be a predictor for developing chronic postoperative pain after TKR.^10 11^

Validated proxies, including questionnaires, neuroimaging and quantitative sensory testing (QST), have been used to examine pain sensitisation. However, a gold standard to diagnose pain sensitisation in a clinical setting is lacking, and individualised mechanism-based treatment in knee OA remains a pressing need.

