### Sample size

This is a feasibility study aiming to provide first proof of concept and descriptive statistics to power a future diagnostic trial. We aim to recruit 50 participants (25 to each group). This would be a large enough sample to assess the feasibility and inform a main trial based on statistical methodological papers providing recommendations about sample size requirements for feasibility and pilot studies.^17–19^

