### Randomisation procedure and concealment of allocation

Eligible participants will be randomised in a 1:1 allocation ratio. An online computer service (SealedEnvelope.com) will be used for stratified randomisation to either intra-articular injection of bupivacaine or sodium chloride 0.9%. This facility generates codes that are concealed from the research team to either group. To mitigate against risk of allocation imbalance with respect to whether pain is predominantly centrally or peripherally driven, stratification will be based on the scores of the Central Aspects of Pain in the Knee (CAP-Knee) questionnaire, which will be sent to participants before the research visit. Participants will be randomised on a 1:1 allocation basis to either bupivacaine or placebo. To ensure blinding of the investigators to the participant’s group assignment, an authorised research nurse will prepare the allocated treatment. The randomisation schedule will be embedded by the research nurse in a secure password-protected folder to achieve allocation concealment.

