### Statistical methods

Considering the feasibility nature of the study, no formal hypothesis tests will be performed to statistically compare the two study arms and descriptive statistics will be presented. Appropriate parametric or non-parametric statistics will be used according to the data characteristics.Summary statistics will be used to evaluate feasibility objectives such as the feasibility to recruit, timing measurements, to describe the sample and to inform the future main trial by providing power and sample size calculation. Participant acceptability feedback will be qualitatively synthesised using thematic analysis.Primary and secondary outcomes will be descriptively summarised by group as follows:Correlations between the change of pain score and QST measurements at baseline and after intra-articular injection with bupivacaine or placebo.Correlations between the change of pain score and brain network activity at baseline and after intra-articular injection with bupivacaine or placebo using predefined seeds in the pain processing regions.Correlations between the change of pain score and the level of joint damage quantified by MOAKS and measured at baseline.Estimates of between-group effect will be reported as estimates with 95% CIs without p values.In view of the exploratory nature of the study, missing data will not be imputed. The proportion of missing data for each outcome will be described.Differences in effects will be reported descriptively for primary and secondary outcomes between the following subgroups:Based on the stratification variable according to CAP-Knee Questionnaire scores with respect to whether pain is predominantly centrally or peripherally driven.The patients will be divided into responders and non-responders based on a cut-off value of ≥17 mm reduction in VAS post injection.^39^

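### The planned central-versus-peripheral comparison uses CAP-Knee only in categories; an estimate on the continuous score should be added beside it

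*Protocol article*

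**What the plan says.** Under Randomisation procedure and concealment of allocation, participants complete CAP-Knee before the visit and "stratification will be based on the scores of the Central Aspects of Pain in the Knee (CAP-Knee) questionnaire". A pre-injection score therefore exists for everyone randomised.

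Statistical methods brings that stratification into the analysis: "Differences in effects will be reported descriptively for primary and secondary outcomes between the following subgroups", the first of which is "Based on the stratification variable according to CAP-Knee Questionnaire scores with respect to whether pain is predominantly centrally or peripherally driven". The wording implies two levels, but neither the number of levels nor the cut is given.

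The same section lists correlations of pain change with QST, brain network activity and MOAKS. It lists none with CAP-Knee or any other questionnaire. The Objectives section does include questionnaires among the sources of indicators whose correlation with analgesic response will be explored, and CAP-Knee is one of the questionnaires named under Psychometric questionnaires.

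The setting is descriptive: "no formal hypothesis tests will be performed to statistically compare the two study arms and descriptive statistics will be presented", and "Estimates of between-group effect will be reported as estimates with 95% CIs without p values". On size: "We aim to recruit 50 participants (25 to each group").

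**The concern.** Stratified randomisation needs the score in categories; the analysis does not. Once the score is cut, all participants on one side count as alike, and two people just either side of the cut are contrasted as if they differed in kind. The Rationale concedes that no established boundary is available: "However, a gold standard to diagnose pain sensitisation in a clinical setting is lacking".

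The planned main trial is about whether the response to bupivacaine depends on central pain, and this study is meant to supply the figures for designing it. With 50 participants, a difference between subgroups in the bupivacaine-placebo effect is among the least precise things it can estimate. If that difference is estimated only between categories, it will usually be less precise than the data allow, and it will depend on where an unstated cut falls. The list of analyses also falls short of the secondary objective, because no questionnaire score is related to response.

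**Working it through.** The article states no power, SD, effect size or information figure for this comparison, so there is no planned figure to reproduce. The check asks how much information on effect modification a two-way split keeps, relative to the continuous score.

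**Inputs**
- n = 50, 25 per arm (Sample size).
- Share above the cut, p: not stated. Assumed range 0.30 to 0.50. The lower value borrows a background figure from the Rationale ("Central sensitisation was estimated to be present in about 30% of patients with OA"), which is not a CAP-Knee cut. The upper value is a median split.
- Score distribution and shape of the effect: not stated. Base case is a normal score and linear effect modification; alternatives follow.

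**Base case.** Efficiency = φ(z)² / [p(1−p)], where z is the normal quantile with a share p above it. Because treatment is randomised independently of the score, the same ratio applies to the treatment-by-score interaction.
- p = 0.50: z = 0, φ = 0.3989; 0.3989² / 0.25 = 0.637. Loss 36%.
- p = 0.30: z = 0.524, φ = 0.3477; 0.3477² / 0.21 = 0.576. Loss 42%.

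In participants: 50 × 0.637 = 31.8 and 50 × 0.576 = 28.8, so the split is worth about 32 or 29 of the 50. In interval width, on a common scale: 1/√0.637 = 1.25 and 1/√0.576 = 1.32, so 25% to 32% wider.

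Simulating the interaction model at n = 50 (4,000 trials per setting) gave efficiencies of 0.63 for the median split and 0.55 for the 30/70 split, close to the formula.

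**Other score shapes, effect still linear**

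| Score | Efficiency formula | p = 0.50 | p = 0.30 |
|---|---|---|---|
| Uniform | 3p(1−p) | 0.75 (loss 25%) | 0.63 (loss 37%) |
| Exponential | (p ln p)² / [p(1−p)] | 0.48 (loss 52%) | 0.62 (loss 38%) |

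**True step exactly at the cut.** The split then loses nothing and the linear score is the worse model. In simulation the efficiency ratio favoured the split by 1.6 (p = 0.50) and 1.9 (p = 0.30).

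**Two true classes measured by a noisy score.** This lies between the line and the step. Assume the score is normal within each class with class means d SDs apart, the effect depends only on true class, and 30% or 50% of participants are truly central. The efficiency of the split relative to the linear score is corr(split, class)² / corr(score, class)².
- Best possible cut: 73% to 75% at d = 1, 83% to 86% at d = 1.5, 93% to 97% at d = 2. The split overtakes the linear score by d = 2.5 (102% to 106%).
- 30% truly central but a median cut: 64% to 71% for d from 1 to 3.

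**The case against.** The strongest objection concerns the question being asked. The Abstract and Evidence gap frame the main trial as a comparison of people with and without evidence of central sensitisation, and the Hypothesis section expects the response to reveal two groups. Effects by stratum are then the figures the main trial needs, and a per-SD slope answers a different question. This stands, and it is why the subgroup contrast should not be replaced or demoted. It does not show that the split loses nothing: that needs a step at the cut actually used, or well-separated classes with a well-placed cut. CAP-Knee is a proxy, and the cut is not stated.

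A reader might infer that 36% to 42% of the information is discarded as a matter of fact. The documents do not support that. The score distribution, the linear shape and the cut are all assumptions, and other choices move the figure from 52% down to zero.

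A reader might also infer lost power. That does not fit either: no tests are planned, and the article says the study is not meant to test the main-trial hypothesis. The consequence is a wider interval around an exploratory estimate.

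Nor is the score lost to the study. It is collected, and the secondary objective covers questionnaire indicators. It is set aside in this one comparison and missing from the list of correlations.

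Finally, the modelling of a covariate is often left to the full protocol or SAP, neither of which is shown. That is fair for a bare omission. Here, though, the article names the form of the comparison, and its list of correlations does not match its own objective.

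**Conclusion.** The point holds in a limited form. Statistical methods compares bupivacaine effects only between categories of CAP-Knee and lists no analysis of the score, although the score is available before randomisation and the secondary objective calls for relating response to questionnaire indicators.

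The 58% to 64% of information kept, and the interaction CI 25% to 32% wider, rest on three assumptions that are not in the documents: a roughly normal score, linear effect modification, and 30% to 50% of participants above the cut. Neither the line nor the step can be assumed in advance, which is a reason to report both views of the data. Nothing here invalidates the planned subgroup display or bears on the feasibility objectives.

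**What to change.** Keep the CAP-Knee strata for randomisation and keep the planned descriptive subgroup contrast. In Statistical methods, add beside it:

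- an arm-by-CAP-Knee estimate with the pre-injection score as a continuous linear term, reported as the difference in bupivacaine-placebo effect on VAS change per SD of score, with a 95% CI and no p value;
- a scatter plot of VAS change against the pre-injection score, by arm, so that readers can judge whether the relation looks like a line or a step.

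This also brings the listed analyses closer to the secondary objective. It takes a sentence or two of text, one model and one figure, with no new data or participants. The drawback is one more exploratory estimate that assumes linearity; the text should say so and refer to the plot.

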### Hypothesis

For the future main trial, the hypothesis is that the analgesic response to a peripherally targeted intervention aiming to reduce knee pain will reveal two groups. The non-responders group will be patients with predominantly centrally driven pain characteristics, who will show less analgesic response to the peripherally targeted intervention while the responders group will be patients with predominantly peripheral pain who will show a greater analgesic response to the peripherally targeted intervention. Both groups will respond similarly to placebo. However, this feasibility study is not intended to test the hypothesis of the main trial.

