### Outcomes

#### Primary outcome measures

The change in pain score using a 100 mm VAS during the 6MWT from baseline to 1 hour after intra-articular injection with bupivacaine or placebo.The change in pain score using the VAS at rest from baseline to 1 hour after intra-articular injection with bupivacaine or placebo.

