#### Secondary outcome measures

QST: the change scores of PPT, TSP and CPM from baseline to post intra-articular injection with bupivacaine or placebo.fMRI of the brain: the change in brain network activity from baseline to post intra-articular injection with bupivacaine or placebo.MOAKS^35^: the level of joint damage quantified by MOAKS and measured at baseline.Feasibility assessment: the number and percentage of eligible participants who are recruited and randomised to the study from the date of recruitment opening until the date of recruitment closing, as well as protocol completion rates and missing data rates.Feasibility assessment: evaluation of effective randomisation of participants to the study arms using a study-specific checklist and assessment of the randomisation protocol throughout the study.Feasibility assessment: a study-specific questionnaire will be administered to participants to assess the acceptability of the study at the end of the research visit.

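### Responder status (a VAS fall of 17 mm or more after injection) is used as a subgroup for effects on outcomes that are themselves VAS changes: the VAS gap is built in, and any arm effect reported inside the split is biased

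*Protocol article*

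**What the plan says.** Under Statistical methods, the protocol article states: "Differences in effects will be reported descriptively for primary and secondary outcomes between the following subgroups". Two subgroup factors follow, under the same sentence and without separate handling.

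- **CAP-Knee stratum.** This is fixed before injection. The randomisation section says that "stratification will be based on the scores of the Central Aspects of Pain in the Knee (CAP-Knee) questionnaire", and that the questionnaire is sent out before the visit.
- **Responder status.** "The patients will be divided into responders and non-responders based on a cut-off value of ≥17 mm reduction in VAS post injection".

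The two primary outcomes are "The change in pain score using a 100 mm VAS during the 6MWT from baseline to 1 hour after intra-articular injection with bupivacaine or placebo" and "The change in pain score using the VAS at rest from baseline to 1 hour after intra-articular injection with bupivacaine or placebo". The secondary outcomes include "the change scores of PPT, TSP and CPM from baseline to post intra-articular injection with bupivacaine or placebo", change in brain network activity, and "the level of joint damage quantified by MOAKS and measured at baseline".

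The Statistical methods section also says that there will be no formal tests between arms, and that between-group effects will be given as estimates with 95% CIs and no p values.

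**The concern.** A subgroup factor for treatment effects should be something that treatment cannot change. CAP-Knee meets that condition. A fall in VAS after injection does not: it is a dichotomised version of the outcome being summarised, and it is measured after randomisation. This has two consequences, depending on how the sentence is read.

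1. If VAS change is summarised by responder status, the groups differ because they were defined to differ. The gap carries no information about bupivacaine or pain mechanism.
2. If bupivacaine and placebo are compared within responders and within non-responders, randomisation no longer protects the comparison. Placebo patients labelled as responders are those with large falls for other reasons (placebo response, regression to the mean, measurement noise), and they are set against a differently selected bupivacaine group.

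The label also means different things in the two arms. In the placebo arm it says nothing about how a patient would respond to bupivacaine. At stake is whether readers take a built-in gap for evidence of two pain types, or a distorted within-split difference for the drug effect.

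**Working it through.** **Inputs from the protocol article:** cut-off 17 mm; 25 patients per arm; both primary outcomes are VAS changes. The article gives no SD, mean change or effect size, so there is no plan figure to reproduce.

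**Assumed:** VAS reduction D is normal with mean m and SD s. The range shown is s = 15, 20, 25 mm. These values illustrate; they do not predict.

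**Formulas.** With a = (17 − m)/s, φ the normal density and p = P(D ≥ 17):
- mean among responders = m + s·φ(a)/p
- mean among non-responders = m − s·φ(a)/(1 − p)

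**Step 1: built-in gap, no drug effect.** For m = 10 and s = 20, a = 0.35, φ(a) = 0.375 and p = 0.363. Responders average 10 + 20 × 0.375/0.363 = 30.7 mm and non-responders 10 − 20 × 0.375/0.637 = −1.8 mm, a gap of 32.4 mm before rounding. For mean falls of 10 to 20 mm:

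| SD (mm) | Gap (mm) | Placebo patients labelled responders |
|---|---|---|
| 15 | 24 to 25 | 32% to 58% |
| 20 | 32 | 36% to 56% |
| 25 | 40 | 39% to 55% |

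At m = 10 and s = 20 that is about 9 of 25 placebo patients (25 × 0.363). The full gap applies to the VAS that sets the label. On the other VAS, with equal SD and correlation ρ, the null gap is ρ × 32.4, or 16.2 mm at ρ = 0.5.

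**Step 2: arm difference inside the split, same effect in every patient.** Mean falls are 25 mm (bupivacaine) and 10 mm (placebo), s = 20, true difference 15 mm.
- Responders: 36.2 − 30.7 = about 5.6 mm
- Non-responders: 3.6 − (−1.8) = 5.4 mm

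SD 15 and 25 give 5.5 to 5.6 and 5.4 mm. With a true 10 mm and s = 20, the results are 3.4 and 3.9 mm. With a true effect of zero, both within-split differences stay at zero.

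**Step 3: two response types.** Suppose half of patients gain 30 mm from bupivacaine and half gain nothing, with placebo mean 10 and s = 15. The true average effect is 15 mm.
- Placebo: p = 0.320, with means 26.7 (responders) and 2.1 (non-responders).
- Bupivacaine patients who gain: mean 40, p = 0.937, with means 42.0 and 10.5.
- Bupivacaine responders: (0.5 × 0.937 × 42.0 + 0.5 × 0.320 × 26.7)/0.629 = 38.1 mm. The arm difference is 38.1 − 26.7 = about 11.3 mm.
- Bupivacaine non-responders: (0.5 × 0.063 × 10.5 + 0.5 × 0.680 × 2.1)/0.371 = 2.8 mm. The arm difference is 2.8 − 2.1 = 0.7 mm.

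The 11.3 mm is neither the average effect (15) nor the effect in those who gain (30), but it is shrunk less than in step 2. Those who gain make up 0.469/0.629 = 75% of bupivacaine responders and 0.031/0.371 = 8% of bupivacaine non-responders.

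**Step 4: other post-injection outcomes.** For an outcome with true effect 10 mm, SD 20 and correlation ρ with the VAS that sets the label, the arm difference inside the split is 10 − ρ × (10 − within-split VAS difference). At ρ = 0.5 this is 10 − 0.5 × (10 − 3.4) = 6.7 in responders and 10 − 0.5 × (10 − 3.9) = 6.9 in non-responders. At ρ = 0.3 it is about 8; at ρ = 0.7 it is 5.4 and 5.7. QST and fMRI changes have other units, so these figures show the pattern only. MOAKS is measured before injection and has no arm effect to bias.

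**The case against.** The plan does not say in so many words that bupivacaine will be compared with placebo inside each responder group. The responder sentence says only that patients will be divided. Comparing baseline QST, imaging or MOAKS between responders and non-responders would fit the secondary objective of relating analgesic response to central and peripheral indicators, and it would be legitimate. This stands, so the bias in arm effects is stated here as conditional. It does not rescue the sentence: the split is listed for effects on the primary outcomes as well, and those are VAS changes.

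The study is descriptive, without p values, and says that it does not test the main trial's hypothesis. That limits the consequence. It does not remove bias from an estimate or its CI.

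A reader might go further in four ways that the documents do not support:

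- **That about two-thirds of any true effect is lost.** This holds in step 2, where every patient has the same effect. The Hypothesis section expects two response types, and step 3 then shows less shrinkage among responders.
- **That the label cannot identify peripherally driven patients.** In the bupivacaine arm it is noisy but informative (75% against 8% in step 3). The criticism holds in full only for the placebo arm.
- **That the main trial's sample size will be wrong.** No section says that the responder split feeds that calculation, and whole-arm estimates are planned as well.
- **That "Both groups will respond similarly to placebo" is contradicted by the analysis.** That sentence states the future trial's hypothesis and is not evidence of an analysis error.

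**Conclusion.** The point holds in limited form and should be fixed. Responder status is not a valid subgroup for VAS outcomes or for treatment effects.

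- **VAS change by responder status:** the gap is created by the definition, at about 24 to 40 mm with no drug effect, under normal change scores with SD 15 to 25 mm.
- **Arm effects inside the split, if reported:** biased whenever the drug works. A true 15 mm appears as about 5.5 mm in each half under a constant effect and SD 20 mm; the size depends on how effects vary between patients.
- **QST and fMRI changes:** partial bias that grows with their correlation with VAS change.
- **Unaffected:** whole-arm estimates, the CAP-Knee subgroup, and descriptions of baseline features such as MOAKS by responder status.

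The direction of these results rests on the plan's own definitions. The millimetre figures rest on assumed SDs and effects.

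**What to change.** In Statistical methods:

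1. Remove responder status as a subgroup for VAS outcomes and for treatment effects.
2. Report a reduction of at least 17 mm as a binary outcome: the proportion in each arm and the risk difference with its 95% CI, saying which VAS (rest or walking) defines it.
3. Use responder status only to describe pre-injection characteristics (CAP-Knee, PPT, TSP, CPM, MOAKS, baseline brain connectivity), separately within each arm.
4. Keep the CAP-Knee stratum as the only subgroup factor for treatment effects.

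The cost is a few lines of analysis wording. Data collection, sample size and randomisation do not change.
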